**OBJECTIVES, DESIGN, AND HYPOTHESES**

The purpose of this study is to examine the efficacy, feasibility, and acceptability of videoconferencing-delivered CBT for anxiety disorders in LGBTQ+ adults. A CONSORT-R compliant, two-group, randomised control feasibility trial (RCT) will examine the research questions. The hypotheses for this study are below:

1. Videoconferencing-delivered, standard CBT will result in significant reductions in symptoms with a large between-group and within-group effect size at post-treatment and three-month follow-up.
2. Videoconferencing-delivered, LGBTQ-adapted CBT will result in a similar degree of symptom reduction when compared to standard CBT.
3. Videoconferencing-delivered standard CBT and LGBTQ-adapted CBT will be feasible to deliver to LGBTQ+ adults with diagnosed anxiety, as assessed by at least 80% treatment fidelity (Borrelli et al., 2005), at least 80% retention following the waitlist period (Fernandez et al., 2015).
4. Videoconferencing-delivered CBT will be acceptable to LGBTQ+ adults with diagnosed anxiety disorders, as assessed in qualitative semi-structured exit interviews and by at least 70% treatment retention and questionnaire completion at follow-up (Fernandez et al., 2015).

The study’s design has two groups:

**Group 1 (*n* = 26): Immediate treatment group.** Group 1 will immediately receive standard, unadapted CBT delivered via videoconferencing. This treatment will be delivered via Zoom. Participants in Group 1 will receive one 50-minute session per week for eight weeks.

**Group 2 (*n* = 26) Waitlist control group.** Group 2 will commence the treatment after a waitlist period of nine weeks, and will recomplete screening measures and their diagnostic interview. Group 2 will receive a similar CBT treatment delivered via Zoom, but this treatment has been tailored to account for the unique challenges experienced by LGBTQ+ people (Pachankis, 2014). LGBTQ-adapted treatment has been shown to be efficacious in previous trials (Pachankis et al., 2015; Pachankis et al., 2020).

A waitlist control was chosen given no studies have currently investigated standard CBT for internalising disorders in LGBTQ+ individuals. As such this study is designed as a feasibility study, phase 1 clinical trial.

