**3. Randomisation**

If a participant meets all the study criteria, then they will be randomised to either an immediate treatment group or a waitlist control group (WLC). Randomisation will be conducted using a random number generator via the website www.random.org to ensure unbiased selection. Assessing clinicians will not be aware of the randomisation status of participants and will be advised of their participants’ group randomisation by the Principal Investigator. Participants will be advised of their group assignment, along with their acceptance into the study, via email. An email with a REDCAP link to pre-treatment questionnaires will be sent to participants in both groups to be completed. After the competition of these questionnaires, participants in group 1 (immediate treatment) will be called to schedule treatment to begin as soon as possible. Participants in group 2 (waitlist control) will be called 9 weeks later to complete the diagnostic interview and self-report questionnaires and schedule treatment as soon as possible.

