It is noted by the researchers that most people presenting for treatment with an internalising disorder have experienced their symptoms for several years (Patton et al., 2014). This means that participants have likely consulted multiple medical or mental health clinicians without complete or partial remission of symptoms. Minority stressors for LGBTQ+ participants are also by nature managed by LGBTQ+ people chronically in the long-term (Meyer, 2003), and thus unlikely to need urgent care within the eight-week period of the waitlist, while receiving treatment for eight weeks, or during follow-up. In any case, this study is not a crisis service, and participants who need urgent care will be referred out at assessment to seek urgent psychiatric care or support from their primary care provider.

Management of risk will be ongoing throughout the project. Importantly, all participants will be made aware of what steps they can follow in a mental health emergency in multiple communication modes at multiple timepoints. For example, which services to contact and what to do in a mental health crisis is outlined in (1) the PICF; (2) a safety plan provided to all clients at the beginning of treatment; (3) in every email communication with participants. Secondly, participants' responses to their questionnaires will be monitored, meaning that deteriorating or consistently elevated symptoms will trigger the research team to contact the participant to encourage contact with their health care team or emergency services. All communication between participants and the research team will be documented.

Assessed for eligibility.

Participants who do not meet criteria will be excluded.

Three-month follow-up diagnostic assessment.

Post-treatment diagnostic assessment and self-report questionnaires.

Qualitative Interviews (n = 10)

Allocated to immediate intervention with Unified Protocol (n = 26).

Post-treatment diagnostic assessment and self-report questionnaires.

Qualitative Interviews (n = 10)

Three-month follow-up diagnostic assessment.

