**INCLUSION/EXCLUSION CRITERIA**

The RCT and qualitative semi-structured interviews will utilise the following inclusion criteria:

(1) Presently residing in Australia;

(2) Aged 18 years or over;

(3) Fluent in English;

(4) Meets criteria for an anxiety disorder as either the primary diagnosis or co-occurring with a depressive disorder and the disorder is of at least ‘moderate severity’ (defined as a score of 4 on the DIAMOND module severity measure);

(5) Medication-free or on a stable dose (8 weeks) of psychotropic medication; and

(6) Not presently receiving regular psychological services for their anxiety symptoms (defined as sessions at least once a week with a qualified mental health professional);

(7) Identify as LGBTQ+; and

(8) Have access to a private location to complete the treatment for the duration of the study.

The RCT and qualitative semi-structured interviews will utilise the following exclusion criteria:

(1) Suicide risk as assessed by item 9 of the PHQ-9 (a score of 2 or above) at baseline, or the C-SSRS, or a response of ‘yes’ to item 1-3 of the risk questionnaire, or via clinician judgement during the diagnostic interview.

(2) Engagement in non-suicidal self-injury in the past 12 months;

(2) Daily use of alcohol or illicit drugs (meaning illegal drugs, pharmaceutical drugs used outside of their prescribed or intended use, and other substances inappropriately used);

(3) The presence of a schizophrenia spectrum disorder as assessed by the DIAMOND semi-structured clinical interview;

(4) Any significant cognitive/intellectual impairment as assessed during the diagnostic interview;

(5) A medical condition that may interfere with treatment;

(6) No access to a computer with a camera and stable internet on a regular basis;

(7) Is not willing to engage in treatment on a regular basis using internet-videoconferencing software;

(8) Does not explicitly identify as LGBTQ+;and

(9) Does not indicate any anxiety disorder symptoms on the DIAMOND Self Report screener.

Additionally, participants will need to have attended at least one session of treatment to be invited to the qualitative semi-structured interviews.

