**ANALYSIS PLAN**

To meet the study’s aim (i.e., to understand if the treatment is efficacious for reducing symptoms of anxiety disorders ), the following analyses will be conducted. The main analyses looking at treatment outcomes from the RCT will be carried out using conservative intention-to-treat principles and using mixed-linear models analyses to handle missing data. Mixed-models are a robust statistical approach for analysing longitudinal clinical trial data and these analyses will employ an appropriate covariance structure and maximum likelihood estimation, which provides unbiased estimates in the case of missing data, under the assumption that data is missing at random. These analyses account for the effect of missing data, thus additional participant recruitment to account for drop-out rates is not warranted. Using this dataset, other appropriate analyses arising from secondary papers will also be conducted. Participants have been informed in the PICF that other secondary data analyses will be conducted on the data that they provide during their participation in the research trial. This may include intersectional moderator analyses of treatment efficacy based on person-level stigma moderators from the minority stress model to inform further treatment adaption needs (Barrera & Castro, 2006; Meyer, 2003). Comparisons between the standard treatment and the LGBTQ-affirmative CBT protocol will be compared using benchmarking analyses (Minami et al., 2008).

To understand the treatment’s efficacy, clinically significant change will be measured using three methods. Diagnostic change will be assessed from pre- to post-treatment and at follow-up using the DIAMOND structured interview. Treatment response will be measured using the reliable change index (RCI) of Jacobson and Truax (1991) to understand which change on the OASIS is not attributable to measurement error, but rather is statistically reliable. Any increase in symptoms by the RCI magnitude of change will be defined as deterioration in this trial. Clinically significant change at post-treatment and to follow-up will be defined as a score below the cut score of 8 on the OASIS (Campbell-Sills et al., 2009).

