**REPORTING OF ADVERSE EVENTS**

Regular team meetings are conducted between the team and treatment integrity is monitored by registered psychologists. Participants are monitored regularly throughout treatment during their treatment sessions and via self-report questionnaires, available in Appendix P. The Chief Investigator and Student Investigator have completed the good clinical practice training at UTS.

As this study is not trialling the effects of a pharmaceutical drug or medical equipment but rather the effects of talk therapy, potential adverse events to endanger participant safety are rare and unknown (Duggan et al., 2014). As such, no significant safety issues (SSI) or serious adverse events (SAEs) are expected in this study, but may still occur, and so a log will be kept of all SSIs or SAEs that arise including their potential relatedness to the treatment. In all adverse events, the treating clinician will take steps to ensure the participant’s immediate health and safety using clinical judgment in collaboration with the principal investigator. SAEs in this study are defined as hospitalisation, death, adverse events resulting in permanent harm or disability, or life-threatening or otherwise medically significant risks as assessed by the clinician. When detected, SAEs will be reported to the Health and Medical Research Ethics Committee by the principal investigator within 24 hours along with details of the event and actions taken to mitigate risk from the adverse events log. SSIs will be defined as marked deterioration in symptoms measured by a decrease in self-report questionnaires of a magnitude denoted by the reliable change index (Jacobson & Truax, 1991), clinician clinical judgement, or a combination of both. Once detected, participant risk will be assessed as is standard in clinical practice. Participants whose risk level escalates or whose symptoms markedly deteriorate will be encouraged to contact their health professional team, such as their GP, or emergency services, and refer to their safety plan made at the beginning of treatment.

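### The safety-issue definition measures deterioration by a fall in symptom scores (wrong direction, no scale named), and PHQ-9 item 9 has no trigger after entry

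*Protocol*

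**What the plan says.** Under Reporting of Adverse Events, an SSI is marked symptom deterioration, measured by "a decrease in self-report questionnaires of a magnitude denoted by the reliable change index", by clinician judgement, or by the two together. Once an SSI is detected, the participant's risk is to be assessed. The section adds: "Participants whose risk level escalates or whose symptoms markedly deteriorate will be encouraged to contact their health professional team".

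The Analysis Plan applies the same index to the OASIS and states: "Any increase in symptoms by the RCI magnitude of change will be defined as deterioration in this trial".

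On suicide risk, the exclusion criteria list "Suicide risk as assessed by item 9 of the PHQ-9 (a score of 2 or above) at baseline", alongside the C-SSRS, three items of the risk questionnaire and clinician judgement. Table 1 schedules the PHQ-9 again at every assessment after screening: four times in Group 1 and five in Group 2. It marks the C-SSRS and the risk questionnaire at screening only.

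Section 6 of Study Procedures (Managing Study Procedure Risks) says that questionnaire responses are monitored and that "deteriorating or consistently elevated symptoms will trigger the research team to contact the participant".

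**The concern.** The SSI sentence is an operating rule. It decides which score changes are recorded as safety issues and which lead to a risk assessment. As worded, its only measurable criterion is met by improvement and not by worsening. It conflicts with the Analysis Plan and does not identify the questionnaire, although the trial uses more than ten.

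The second matter is one of coverage. The protocol regards an item 9 score of 2 or more as risk enough to keep someone out of a remote trial that is not a crisis service. After entry the same answer on the same form has no stated consequence. The only score-based trigger left is the RCI, which is built for change in a total score and not for one safety item. Whether, and how soon, a later answer of 2 or 3 leads to a risk assessment then depends on general monitoring and individual judgement, so it may differ between participants.

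**Working it through.** The protocol gives no figure to reproduce. The first three steps compare its sections; the fourth is an illustration on assumed inputs.

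**1. Direction.** From Study Measures:
- OASIS and ODSIS items run from 0 (little or none) to 4 (extreme).
- PHQ-9 items run from 0 to 3 with increasing symptom frequency.
- The dimensional anxiety scales use items scored 0 to 4. Higher means more frequent or more severe wherever the direction is described; for the panic scale it is not spelled out.
- The Analysis Plan counts an OASIS score below 8 as clinically significant change.

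On these scales a decrease is improvement. A fall would be unfavourable on the Client Satisfaction Questionnaire, but that does not measure symptoms.

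**2. Scale.** The Analysis Plan ties the RCI to the OASIS. The SSI sentence refers only to self-report questionnaires in general. No RCI value, SD or reliability is given in either place.

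**3. Consequence.** The sentence after the SSI definition makes detection the starting point for a risk assessment. SAEs have a 24-hour reporting limit; SSIs have no time limit.

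**4. Could an RCI pick up item 9?** An eligible participant scores 0 or 1 on item 9 at screening. Reaching 2 or 3 is a rise of 1, 2 or 3 points. If the OASIS RCI is meant, item 9 does not enter it. If the PHQ-9 total is meant, RCI = 1.96 × √2 × SD × √(1 − r). With assumed SD and reliability r:

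| SD | r = 0.80 | r = 0.85 | r = 0.90 | r = 0.92 |
|---|---|---|---|---|
| 3 | 3.72 | 3.22 | 2.63 | 2.35 |
| 4 | 4.96 | 4.29 | 3.51 | 3.14 |
| 5 | 6.20 | 5.37 | 4.38 | 3.92 |
| 6 | 7.44 | 6.44 | 5.26 | 4.70 |

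Holding the other eight items fixed, a rise of 1 or 2 points reaches the RCI in 0 of 16 cells. A rise of 3 points reaches it in 2 of 16 (SD 3 with r = 0.90 or 0.92). At r = 0.95, outside this grid, SD 3 gives 1.86 and SD 4 gives 2.48, so a 2-point rise would suffice in the first case and a 3-point rise in both. No combination examined is reached by 1 point. Other items may rise at the same time and carry the total past the RCI, so the table shows only what item 9 can do alone.

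**5. Other routes.**
- Questionnaire monitoring (section 6) names no item, score or time.
- Clinician judgement is enough on its own for an SSI.
- Table 1 marks a clinician-rated CGI-S at every assessment, and a DIAMOND interview at post-treatment, at follow-up and before Group 2 starts treatment.
- Crisis steps appear in the consent form and in every email to participants.
- The remaining safeguard is "a safety plan provided to all clients at the beginning of treatment", which Group 2 reaches only after the wait.
- The design section says Group 2 "will recomplete screening measures and their diagnostic interview" after the wait. Table 1 repeats neither the C-SSRS nor the risk questionnaire then, and neither place attaches an item 9 rule.

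**The case against.** The strongest reply is that the word is a slip in a sentence whose subject is marked deterioration, and that the Analysis Plan gives the direction outright. That is largely right. A reader might infer that the trial would log its responders as safety issues and overlook those who worsen. The documents do not support this, because a responder has not deteriorated and so does not meet the definition as a whole. What stands is that the measurable criterion contradicts the term it is meant to measure.

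The second reply is that the protocol never gives the RCI the task of catching suicidal answers, and that other routes exist. This also has force. A reader might infer that a later item 9 answer of 2 or 3 would go unseen. The protocol does not show that: monitoring, clinician ratings, interviews and crisis information in every email all apply, and how often an answer would be missed cannot be estimated. What stands is that none of these routes names the item, a score or a response time.

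Third, an item 9 rule would do little for the waitlist. Group 2 "will be called 9 weeks later to complete the diagnostic interview and self-report questionnaires", and Table 1 schedules no PHQ-9 between weeks 0 and 9, so the rule could not act in that interval. It could act on the week-0 form. Because Table 1 labels that Group 2 column as baseline, the entry threshold might be thought to cover it, but the form is completed after randomisation.

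Finally, item-level alerts often sit in a separate risk procedure. The appendices are not available here and may contain one, although the protocol text cites none with an item 9 cut-off.

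**Conclusion.** The SSI definition is wrong as written. Its direction is reversed for the symptom scales, it contradicts the Analysis Plan, and it leaves the scale unnamed. This rests on the protocol's own wording and needs no assumption. The practical effect is probably small because the intent can be recovered, but a rule that governs the safety log and the ensuing risk assessment should not need interpretation.

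The missing item 9 trigger is a secondary point: an inexpensive safety improvement, not an error. It rests on the entry threshold being limited to baseline and on the repeated PHQ-9 in Table 1. The RCI grid is only an illustration, since the SDs and reliabilities are assumed and the other items are held fixed. It shows that an RCI on the total score is not designed to detect a 1- to 3-point rise in one item. It does not show how many answers would be missed.

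Neither point affects the efficacy analysis. Both should be dealt with in the next amendment.

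**What to change.** **Main change, Reporting of Adverse Events.** Replace the reference to a decrease with *an increase in symptom scores*, and name the scale or scales whose RCI applies: at least the OASIS, to match the Analysis Plan. Keep clinician judgement as a sufficient criterion.

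**Secondary change, the same section and Managing Study Procedure Risks.** Add wording such as: *A PHQ-9 item 9 score of 2 or more at any assessment after entry, including the Group 2 week-0 form, triggers a REDCap alert and a clinician risk assessment within a time set in advance. It is logged as an SSI only if the clinician confirms escalated risk.* Logging should not be automatic: whether every such score is itself a safety issue is a policy choice for the trial's clinicians.

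**Cost.** A short wording amendment and an alert on an item already collected, with no new staff, visits, instruments or analyses. The downside is a few extra review contacts by existing staff, some for answers that prove low risk and some with waitlist participants; these should be recorded by group. The item 9 rule leaves weeks 0 to 9 of the wait as they are now, dependent on the existing safeguards.

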**6. Managing Study Procedure Risks**

We expect participants will experience clinically significant improvements in the symptoms of their anxiety disorder. We also hope that participants will apply the strategies learnt in this trial after study completion, which will likely lead to long-term management of their symptoms. The protocol for treatment encourages participants to not just learn but practice techniques to manage their mental health conditions’ symptoms. It is important to note that in the short-term, participants in cognitive behavioural therapy can experience an increase in symptoms of a mental health condition; however, this is only a temporary increase and will diminish as treatment progresses (Reinecke et al., 2018).

At pre-treatment, post-treatment, and follow-up, participants will be given the option to choose whether their health care provider(s) are made aware of their participation in the study. The templates for these letters are available in Appendix N.

Supporting participant’s safety and emotional well-being is a priority of the researchers. In the rare circumstance that someone requires psychiatric consideration or experiences significant distress, the investigators are mental health clinicians who can assess the situation and refer the person to appropriate services such as their primary physician or emergency services. Given that this study is not trialling the effects of a pharmaceutical drug or medical equipment but rather the effects of talk therapy, potential adverse events are rare. In the unlikely event that adverse events do occur, a log will be kept of adverse events that arise. Serious adverse events (SAEs) involving an immediate physical risk to participant safety will be reported to the Principal Investigator, who will advise the Human Research Ethics Committee of the nature of the SAE and any actions taken to mitigate its effects.

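### Group 2 waits 8 to 9 weeks with no safety plan and no scheduled check, and its outside care is not recorded at the week 9 comparison

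*Protocol*

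**What the plan says.** **Safety plan.** Managing Study Procedure Risks lists three places where participants find out what to do in a crisis: the consent form, "a safety plan provided to all clients at the beginning of treatment", and every email. Reporting of Adverse Events sends participants whose risk rises, or who clearly worsen, to their health team or emergency services, and has them "refer to their safety plan made at the beginning of treatment".

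**Who acts.** "In all adverse events, the treating clinician will take steps to ensure" the participant's immediate safety, "using clinical judgment in collaboration with the principal investigator". More generally, "the investigators are mental health clinicians who can assess the situation and refer the person to appropriate services".

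**Monitoring.** "Participants are monitored regularly throughout treatment during their treatment sessions and via self-report questionnaires". Questionnaire answers are also watched, so that "deteriorating or consistently elevated symptoms will trigger the research team to contact the participant".

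**Timing for Group 2.** The wait is eight weeks in the Summary and in Managing Study Procedure Risks. It is nine weeks in Objectives, Design, and Hypotheses, in Randomisation, in Figure 1 and in Table 1. The Treatment section gives both. Under Randomisation, the next contact after the baseline questionnaires is a call nine weeks later.

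**Protections during the wait.** The Treatment section excludes anyone above low risk, gives all waitlist participants crisis numbers, encourages them to see their GP, and leaves them free to use other services.

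**Serious adverse events.** "SAEs in this study are defined as hospitalisation, death, adverse events resulting in permanent harm or disability", or life-threatening or otherwise medically significant risks as judged by the clinician. A log is kept of those that arise.

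**The concern.** The randomised comparison is treatment against waiting, over weeks 0 to 9. The safety procedures are written for people in treatment: the plan, the monitoring and the first responder all depend on sessions having started. For the waiting half of the sample, one stated escalation step points to a document that does not yet exist, and no scheduled observation could prompt the research team to call.

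A second issue concerns interpretation. Group 2 may use other services while waiting. If that use is recorded in one arm only when the arms are compared, a reader cannot judge how far outside care narrowed the difference.

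**Working it through.** No stated figure has to be reproduced. The check sets the sections side by side and counts entries in Table 1.

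**1. Time without a plan.** Group 2 has 26 participants.
- Full retention: 26 × 8 = 208 and 26 × 9 = 234 person-weeks.
- Lower bound, assuming that only the protocol's 80% post-waitlist retention benchmark stays and that the rest leave at once: 0.80 × 208 = 166.4 and 0.80 × 234 = 187.2, so about 166 to 187.

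This is exposure, not harm. The protocol gives no event rate and none is assumed.

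**2. What remains of the escalation step.** Of the three listed sources of crisis information, two (consent form and emails) are open to Group 2 during the wait and one (the safety plan) is not. The waitlist resources add a further source. Contact with the GP, health team or emergency services is open throughout.

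**3. Scheduled observation strictly between weeks 0 and 9.**

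| | Group 1 | Group 2 |
|---|---|---|
| Questionnaire sets (Table 1) | 1 (mid-treatment) | 0 |
| Treatment sessions | 8, weekly | 0 |

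The outreach trigger works on questionnaire answers. For Group 2 it can respond to the week 0 set and then not again until week 9.

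**4. Responder.** Treatment for Group 2 is scheduled at the week 9 call, so the text gives these participants no treating clinician before then. The principal investigator and the research team can act, but no one is assigned to do so for the wait.

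**5. Risk check at Group 2 week 9.**

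| Instrument | Table 1 | Other text |
|---|---|---|
| PHQ-9, including item 9 | yes | yes |
| DIAMOND interview | yes | yes |
| Risk questionnaire | screening only | repeated, if the Objectives section's statement that Group 2 redoes the screening measures is taken literally |
| C-SSRS | screening only | repeated, since Diagnostic Screening places it within the diagnostic interview |

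The Study Measures text before Table 1 repeats only the pre-treatment measures and the interview. The inconsistency is therefore limited to the last two rows.

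**6. Service Use Questionnaire (SUQ).** The Secondary Measures text gives it at mid- and post-treatment. Table 1 gives it at post-treatment and follow-up.
- Group 1 at week 9 (post-treatment): yes under both.
- Group 2 at week 9 (pre-treatment): no under both. Its first SUQ is at mid-treatment according to the text, or at week 18 according to Table 1.

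**7. Serious adverse event question.** Table 1 schedules none for either arm at any visit.

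**The case against.** The sponsor can fairly say that the choice was reasoned. The protocol argues that these are long-standing problems unlikely to need urgent care during the wait. It excludes people above low risk and, in the full criteria, anyone with self-injury in the past 12 months. It gives crisis information by several routes, and its investigators can assess and refer. This stands, and it is why the stakes are no more than low to moderate. It does not explain why the escalation step relies on a plan that half the sample lacks.

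Several stronger readings are tempting, but the document does not support them:

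- *Group 2 has no safety cover while waiting.* It has the consent form, emails, waitlist resources and the ordinary health services.
- *Suicide risk is not re-checked at week 9.* PHQ-9 item 9 and the clinician-led interview are both repeated, and the eligibility criteria use item 9 and clinician judgement in that interview as risk tests.
- *Serious events in Group 2 are logged only if volunteered.* They can also surface in the week 9 interview. The missing fixed question affects both arms, although Group 1 also has weekly sessions.
- *Group 2 gets no SUQ before week 18.* That is true of Table 1 only.
- *A planned analysis is biased.* The protocol plans no between-arm comparison of events.

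It can also be said that the reference to screening measures in the Objectives section is loose wording, since Questionnaire Administration calls the ordinary questionnaires symptom screeners. That is possible, and then only the C-SSRS entry needs settling. Finally, the SUQ's look-back period is not stated and the questionnaire appendix is not shown, so a later SUQ might reach back over the wait. Even so, it would not be collected alongside the week 9 outcome.

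**Conclusion.** The point holds in limited form and is worth acting on. For the whole randomised period, 26 of 52 participants lack the safety plan that the escalation step invokes, have no scheduled check between weeks 0 and 9, and have no named first responder. At full retention that is 208 to 234 person-weeks; the lower figure of about 166 rests on the assumption about early leavers. At week 9 the only open question about risk re-screening is whether the risk questionnaire and C-SSRS are repeated. Outside care used during the wait is not recorded for Group 2 when the arms are compared, whichever SUQ schedule is followed.

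The reading takes the start of treatment to mean the first session, which for Group 2 follows the wait. It makes no claim about how many events would be missed.

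**What to change.** 1. Make the safety plan with every participant at the diagnostic interview, before randomisation, or by a short call at allocation. Reword Managing Study Procedure Risks and Reporting of Adverse Events to match.
2. Name the principal investigator, or a delegate who is not the outcome assessor, as responder during the wait.
3. Mark the C-SSRS and risk questionnaire at Group 2 week 9 in Table 1, and bring the Study Measures text into line with the Objectives section.
4. At week 9, give both arms the SUQ and a brief serious adverse event question that follows the protocol's own definition and covers the period since the last assessment. Settle the SUQ's other visits at the same time, since the text and Table 1 differ.

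The cost is a few extra minutes per participant at existing contacts, or one short call if the plan is made at allocation. Some plans will be made for people who prove ineligible or leave during the wait. These changes add no scheduled check within the wait; given low-risk entry, a plan in hand and a named responder are a proportionate remedy.
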